### **8.4. Treatment Assignment and Randomization**

#### **8.4.1. Treatment Assignment**

##### **Patient Identification (ID)**

Each patient who signs an informed consent form must receive a patient identification number. Patient identification numbers will be assigned during the screening visit by calling the IVRS for the next available patient number. This patient identification

number will remain the same throughout the study, and will be used by the site to identify the patient. The patient identification number (ID) consists of a 3-digit site number (Site No.) and a 4-digit patient number (Patient No.). The Site No. and Patient No. will be separated by a hyphen. This 8 digit alpha numeric identifier will be manually entered in the "Patient ID" space on the electronic CRF for a given patient.

**Site No. -** Vanda will assign a unique, 3-digit number to each site.

**Patient No. -** The IVRS will assign a 4-digit number to each patient in sequential order by site at the time of the screening visit call. The first (leftmost) will be assigned "1." Example: The first patient who signs a consent form at Site 301 will be assigned the ID 301-1001, the second, 301-1002, etc.

The ID of a patient who discontinues from the study for any reason after having been assigned an ID will not be reassigned. A patient's ID number will remain the same for that patient throughout all phases of the study.

#### **8.4.2. Randomization**

The randomization will be performed using the IVRS, a validated system that automates the random assignment of treatment groups to randomization numbers. The randomization scheme will be reviewed and approved by a biostatistician designated by Vanda. On Night 1, the Investigator or designee will call the IVRS to assign a randomization number which will determine which study medication the patient will be assigned.

## **9. STUDY DRUG MATERIALS AND MANAGEMENT**

### **9.1. Study Drug**

The investigational drug will be 20 mg and 50 mg VEC-162 capsules for oral administration. All capsules will be size 1 and the color will be white opaque. To preserve the study blinding, the placebo capsule will be identical in size, shape, color, and appearance to the VEC-162 capsules.

### **9.2. Study Drug Packaging and Labeling**

Study medication will be provided in HDPE bottles with child-resistant caps containing polyester cushioning and desiccant.

#### **Pre-randomization Phase**

The single-blind placebo for the lead-in period will be provided as individual bottles identified by a unique medication number. Each bottle will contain 10 placebo capsules and the bottle will have a two-part tear-off label. The second part of the label will be torn off at the site and affixed to the patient's source documents before the bottle is dispensed to the patient. Medication labels will comply with US legal requirements and be printed in English. At the screening visit, the IVRS will assign a bottle of single-blind study medication to the patient for the pre-randomization phase of the study.

#### **Randomization Phase**

After eligibility is verified, the Investigator is to call the IVRS on Night 1 to assign a randomization number and medication kit to the patient for the randomization phase of the study. A kit containing 6 bottles of study medication labeled bottle # 1-6 will be assigned to a specific patient. Each bottle within the kit will be labeled with the same medication number. Bottles # 1-5 will contain 10 capsules of 20 mg, or 50 mg of VEC-162 or placebo to provide enough medication for one week of treatment. Bottle # 6 will contain 10 placebo capsules that will be used during the overnight single-blind placebo wash-out.

At each visit, a new bottle of study medication will be used. While at the sleep lab, administration of the study drug will be under the supervision of a member of the study team. The next morning, the bottle(s) will be dispensed to the patient for study medication to last until the next schedule visit. Bottles must be dispensed in consecutive order beginning with bottle #1 (i.e. bottle #1 will be used during and dispensed to the patient at the end of Visit 3, bottle #2 will be used during Visit 4 and bottles #2 and #3 will be dispensed to the patient at the end of Visit 4, bottle #4 will be used during and dispensed to the patient at the end of Visit 5, bottle #5 will be used during and dispensed to the patient at the end of Visit 6, bottle #6 will be used during Visit 7). Patients should be instructed to bring all bottles along with any unused capsules to the study site at his/her next visit.

Each kit will be identified by a unique medication number and have a two-panel blinded label which will comply with the legal requirements of the United States and will be printed in English. The two panel labels on each kit of study medication will have a tear-off portion which must be removed and affixed to the patient's source documents when the kit is allocated to the patient. Each of the 6 bottles in each kit will also have a two-panel blinded label displaying the same medication number as the kit which must also be removed and affixed to the patient's source documents when the bottle is given to the patient.

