Patients will be required to return to the sleep clinic on Nights 8, 22, and 29 ( $\pm 2$  days) for additional nights of PSG recording. At the beginning of each study visit, patients will be required to take a breathalyzer test, a urine pregnancy test for WOCBP, and complete the pre-sleep questionnaire prior to study drug administration. They will receive double-blind study medication 30 minutes ( $\pm 5$  minutes) prior to light off. Lights off should occur within 15 minutes of their scheduled bedtime. Patients will be awakened at the end of the 8-hour sleep episode and will be asked to complete the battery of tests (PSQ, VAS and DSST in this order) 1 hour ( $\pm 15$  minutes) after awakening. At each of these visits, the patients will be dispensed enough medication to last until the next scheduled visit and will be reminded to take one capsule of study medication each night approximately 30 minutes prior to their planned bedtime. Patients will also be given a PSQ to take home with them and instructed to complete the outpatient PSQ on the morning of the next scheduled study visit. Patients will be allowed to leave the sleep clinic after completion of the morning assessments. In addition, on Day 30, patients will be asked to complete the Benzodiazepine Withdrawal Symptom Questionnaire (BWSQ) prior to completing the battery of tests.

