| Adverse Event Query                             |                   | X                                              | X    | X    | X    | X                                                  | X  | X              | X  | X              | X   | X              | X   | X              | X         | X  |
| Prior/Concomitant Med                           | X                 | X                                              |      | X    |      | X                                                  |    | X              |    | X              |     | X              |     | X              | X         | X  |

D= Day; N= Night; PBO= placebo; EOS= end of study; ET= early termination; WOCBP= women of childbearing potential; PSG= polysomnography; PG= Pharmacogenomic; BWSQ= Benzodiazepine Withdrawal Symptom Questionnaire; Med= Medication.

\*These visits have a ± 2-day window. Visit 2 must have two consecutive nights of PSG assessment.

 The informed consent must be sign prior to any study procedure being done.

 Abbreviated- Only required to document changes.

 Body height will only be recorded at screening. Weight will only be recorded at screening, Night 1 and EOS.

 Pregnancy test must be negative prior to dosing.

 At Night -7, only the DSST and VAS will be administered. This session is for practice purpose only. Results will not be used in the analysis.

 The IVRS will be called to assign the patient ID and single-blind PBO bottle at the screening visit. The Investigator will call the IVRS to assign a double-blind medication kit on Night 1. The IVRS will also be called to report patient completion or discontinuation.

 Blood sample for PG assessments should only be obtained if patients sign the optional PG Informed Consent.

 Unused study drug should be collected from the patient and counted at the beginning of Visit 3, 4, 5, 6, and 7.

 Patients will be instructed to complete the PSQ the morning of the next scheduled PSG visit.

 The sleep diary must be completed for at least seven days and returned to the site on Visit 2.

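### At one corner of the visit windows, the single 10-capsule bottle for Visits 5–6 or Visits 6–7 is one capsule short of nightly dosing

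*Protocol*

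**What the plan says.** Visits 4 to 7 are set at Nights 8, 22, 29 and 36 (protocol sections 6.1.2 and 10.2). The footnote to Table 2 says of Visits 2, 4, 5, 6 and 7: "These visits have a ± 2-day window". Visit 3 (Night 1) has no window.

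Section 9.2 states that each of bottles 1 to 5 "will contain 10 capsules of 20 mg, or 50 mg of VEC-162 or placebo to provide enough medication for one week of treatment". A new bottle is opened at each visit and supplies the in-clinic dose as well as the nights at home. For the two late intervals:

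- Visit 5 to Visit 6: "bottle #4 will be used during and dispensed to the patient at the end of Visit 5".
- Visit 6 to Visit 7: "bottle #5 will be used during and dispensed to the patient at the end of Visit 6, bottle #6 will be used during Visit 7".

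Capsules are not carried over. Table 2, footnote 8: "Unused study drug should be collected from the patient and counted at the beginning of Visit 3, 4, 5, 6, and 7". Section 6.1.2 nevertheless says that at each of the visits on Nights 8, 22 and 29 "the patients will be dispensed enough medication to last until the next scheduled visit".

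**The concern.** Ten capsules against a nominal seven-night interval leave three spare. Two adjacent visits that move in opposite directions can lengthen the interval by four nights, one more than the spare. A patient who keeps every visit within its window and takes one capsule each night can therefore run out the night before a recording.

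Two secondary objectives in section 5.1.2 are touched. Before Visit 6, the uncovered night precedes a recording that enters the Nights 22 and 29 average (objective 2, maintenance of effect). Before Visit 7, it matters more. The wash-out is planned as one night, so the recording should capture the first night after abrupt cessation (objective 6). In the short case that first night passes at home, the recording captures the second night off drug, and the end-of-study withdrawal questionnaire (objective 8) shifts with it.

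The lapse would be hard to see afterwards. The visits are in window and the bottle comes back empty. Counted against nights, 10 of 11 doses is 91%, above the 80% at which section 8.3 calls for re-education.

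**Working it through.** **The plan's own figures first.** The synopsis gives treatment of up to 47 days: (7 + 2) lead-in + (35 + 2) double-blind + 1 wash-out = 47, which reproduces. One bottle also covers its stated week: 7 nights needed, 10 capsules supplied.

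**Inputs.** One capsule per night (section 6.1.2); Visit 3 on Night 1; Visits 4 to 7 on Nights 8, 22, 29 and 36, each ±2 days (Table 2); 10 capsules per bottle and the bottle-to-visit allocation (section 9.2); no carry-over (Table 2, footnote 8).

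**Formula.** A bottle opened at one visit must cover that night and every night up to the one before the next visit. Capsules needed = next visit night − this visit night. The largest value allowed has the earlier visit at its lower limit and the next at its upper limit.

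| Interval | Bottles | Longest permitted | Needed | Supplied |
|---|---|---|---|---|
| Visit 3 to 4 | 1 | Night 1 to 10 | 9 | 10 |
| Visit 4 to 5 | 2 and 3 | Night 6 to 24 | 18 | 20 |
| Visit 5 to 6 | 4 | Night 20 to 31 | 11 | 10 |
| Visit 6 to 7 | 5 | Night 27 to 38 | 11 | 10 |

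The lead-in bottle also fits: at most 9 nights from 10 capsules.

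**Which night is uncovered.** Bottle 4 opened on Night 20 is empty after Night 29, so Night 30 has no capsule; the Night 31 dose comes from bottle 5. Bottle 5 opened on Night 27 is empty after Night 36, so Night 37 has none; Night 38 is the placebo wash-out recording.

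**How often.** Each pair of adjacent late visits has 5 × 5 = 25 combinations, with intervals from 3 to 11 nights. Only the 11-night one fails, so 1 of 25 in each interval. The two failures cannot occur in one patient: the first needs Visit 6 on Night 31, the second needs it on Night 27.

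**Total supply.** Bottles 1 to 5 hold 5 × 10 = 50 capsules, against at most 35 + 2 = 37 double-blind nights. The kit is sufficient; only the allocation to intervals falls short.

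**Patients, as illustration only.** The documents give no distribution of visit days. If days were uniform and independent over each window, 1/25 = 4% of patients would be short in each interval. Only active-arm patients lose drug: 324 × 2/3 = 216. Applying the plan's 20% drop-out in full before these visits gives 216 × 0.8 ≈ 173, and 4% of that is about 7 patients per interval. Clustering on the nominal days would make it fewer; lost capsules would make it more.

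**The case against.** **The windows might run from the previous visit.** The longest late interval would then be 7 + 2 = 9 nights and nothing would be short. No section says this, and the synopsis argues against it. Chained windows would allow (7 + 2) + (14 + 2) + (7 + 2) + (7 + 2) = 43 double-blind nights, beyond the stated 35 ± 2. Windows fixed to the numbered nights are the reading that fits.

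**The sentence in section 9.2 is not itself false.** This stands: 10 capsules do cover a week. The conflict is with the section 6.1.2 promise of enough drug to reach the next visit, read against the windows.

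**A skipped night removes the shortfall.** This also stands. Patients are told to take study medication only with at least a 6-hour opportunity to sleep, so some will have a capsule left. The count applies to a patient who doses every night.

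**Bridging with the next bottle.** A reader might infer that a site would fill the gap from the next bottle and so give placebo to an active-arm patient. That cannot happen between Visits 5 and 6, because bottle 5 holds the assigned treatment. Between Visits 6 and 7 the next bottle is the placebo bottle 6, but section 9.2 numbers the bottles and reserves bottle 6 for use at Visit 7. The inference requires a site to break a stated rule.

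**Conclusion.** The inconsistency is real and minor. Within the protocol's own windows, nightly dosing can need 11 capsules where 10 are supplied, in 1 of 25 window combinations for Visits 5–6 and 1 of 25 for Visits 6–7. This rests on windows fixed to the numbered nights, a dose every night, and no return of collected capsules.

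Two larger readings are tempting. One is that 2/25 = 8% of the trial, about 26 of 324 patients, would be affected. That figure depends on an unsupported uniform spread of visit days and counts placebo patients and drop-outs; the documents do not establish the true share. The other is that the rebound objective is not measured as planned. That is so only for active-arm patients at the extreme corner, not for the objective as a whole.

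The primary endpoint (Nights 1 and 8) is untouched, since the first interval needs at most 9 of 10 capsules. No dose on a recording night is lost. Sample size and type I error are not involved.

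**What to change.** Reconcile section 6.1.2, the window and drug-collection footnotes to Table 2, and the bottle allocation in section 9.2, so that the longest interval permitted between Visits 5 and 6 and between Visits 6 and 7 agrees with the supply allotted to it. Whether the scheduling text or the packaging text changes is for the sponsor to decide.

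The cost is about one sentence in one of those places. No analysis or sample-size text needs to change.

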### **9.3. Study Drug Storage**

Drug supplies must be stored in a safe, secure location at 20°C to 25°C (68°F to 77°F), and must be protected from light, heat, and moisture. The storage conditions for study medication will be described on the medication label.

### **9.4. Study Drug Accountability**

Vanda Pharmaceuticals Inc. is responsible for assuring that the quality of the study drug is adequate for the duration of the study.

Study medication should be used in accordance with the protocol, under the supervision of the Investigator or delegated by the Investigator to the site pharmacist or other personnel trained to store and dispense investigational drugs.

The Investigator or a designee is responsible for taking an inventory of each shipment of study medication received and comparing it with the accompanying packing list. The Investigator or a designee will verify the accuracy of the information on the packing list, sign and date the acknowledgement of receipt, retain a copy in the study file, and send a copy to Vanda or its designee.

The Investigator or Co-Investigator(s) must agree to supply study medication only to patients enrolled in the study. Each patient must be given the study medication corresponding to his/her medication code number. It is the responsibility of the Investigator to ensure that a current record of study drug disposition is maintained. Records or logs must comply with applicable regulations and guidelines, and should include:

- Amount of study drug received
- Medication batch number
- Dates of drug inventory movement
- Unique patient identifier
- Amount dispensed to each patient
- Amount returned by each patient
- Initials of person responsible for each drug inventory entry

Accurate recording of all study medication administration (including dispensing and dosing) will also be made in the appropriate section of the patient's electronic CRF and source documents.

Vanda or its designee will instruct the Investigator on the return or destruction of unused study medication. If any study medication was lost or damaged, its disposition should be documented in the patient's source documents as well as the drug accountability record. Study medication supplies will be retained at the clinical site until instructions for return or destruction of the supplies are received from Vanda or its designee.

## **10. STUDY ASSESSMENTS AND RESTRICTIONS**

### **10.1. Pre-Randomization**

#### **10.1.1. Screening Visit**

The following evaluations will be performed **after** the patient signs the informed consent form:

##### **Visit 1 (12 to 21 days prior to Night 1)**

- IVRS call to assign patient ID and a medication bottle
- Prior/current medication
- Collection of patient's demographic information (e.g. date of birth, race, gender)
- Inclusion/exclusion criteria
- Medical, sleep and psychiatric history
- Owl-lark questionnaire
- Vital signs (body temperature, respiratory rate, blood pressure, pulse, weight, and height)
- Full physical exam
- Laboratory evaluations (hematology, biochemistry and urinalysis)
- Full standard 12-lead ECG
- Urine drug screen
- Serum  $\beta$ -HCG for women of childbearing potential (WOCBP), except those who have been postmenopausal for at least 1 year or are surgically sterile
- Dispense outpatient PSQ
- Dispense sleep diary

#### **10.1.2. Single-blind Placebo Lead-in Period**

##### **Visit 2 (7 days $\pm$ 2 prior to Night 1)**

##### **Night -7**

- Review of sleep diary (only data from 7 days immediately preceding Visit 2)
- Collect outpatient PSQ
- Review of inclusion-exclusion criteria
- Vital Signs (body temperature, respiratory rate, blood pressure, and pulse)
- Practice for battery of tests (VAS, and DSST, in this order)

- Breathalyzer
- Urine drug screen
- Urine pregnancy test for WOCBP, except those who have been postmenopausal for at least 1 year or are surgically sterile (result must be negative prior to dosing)
- Pre-sleep questionnaire
- Adverse event query
- Review of concomitant medication
- Administration of single-blind treatment ( $30 \pm 5$  minutes prior to light off)
- Diagnostic PSG (score locally for exclusionary purpose; score will be confirmed by central scoring facility)

**Day -6**

- Vital Signs (body temperature, respiratory rate, blood pressure, and pulse)
- Adverse event query
- Battery of tests (Post-sleep questionnaire, VAS, and DSST, in this order; one hour [ $\pm 15$  minutes] after awakening)

**Night -6**

- Breathalyzer
- Pre-sleep questionnaire
- Adverse event query
- Review of concomitant medication
- Administration of single-blind treatment ( $30 \pm 5$  minutes prior to light off)
- PSG

**Day -5**

- Vital Signs (body temperature, respiratory rate, blood pressure, and pulse)
- Adverse event query
- Battery of tests (Post-sleep questionnaire, VAS, and DSST, in this order; one hour [ $\pm 15$  minutes] after awakening))
- Drug Dispensing for out-patient use (single-blind treatment)
- Dispense outpatient PSQ and instruct patient to complete prior to the next scheduled visit

**Nights -5 ( $\pm 2$  days) to -1; outpatient**

- Take study medication 30 minutes prior to planned bedtime

## **10.2. Randomization Phase**

### **10.2.1. Double-blind Evaluation Period**

#### **Visits 3-6**

##### **Night 1 (Visit 3)**

- Review of inclusion-exclusion criteria
- Collect unused drug, from single-blind placebo lead-in
- Collect outpatient PSQ
- Brief Physical examination (conducted only if patient reports change in health or experiences an AE)
- Full standard 12-lead ECG in triplicate (approximately 5 minutes apart)
- Vital signs (body temperature, respiratory rate, blood pressure, pulse, and weight)
- Urine drug screen
- Urine pregnancy test for WOCBP, except those who have been postmenopausal for at least 1 year or are surgically sterile (result must be negative prior to dosing)
- Breathalyzer
- Randomization through IVRS to assign medication kit (**after** patient meet all inclusion exclusion criteria including negative pregnancy test)
- Laboratory evaluations (hematology, biochemistry and urinalysis)
- Blood draw for optional pharmacogenomic (PG) analysis (if consent is given by the patient)
- Blood draw for PER3 genotyping
- Pre-sleep questionnaire
- Review of concomitant medication
- Adverse event query
- Study medication administration ( $30 \pm 5$  minutes prior to light off)
- PSG

##### **Day 2 (Visit 3)**

- Vital Signs (body temperature, respiratory rate, blood pressure, and pulse)
- Adverse event query
- Battery of tests (Post-sleep questionnaire, VAS, and DSST, in this order; one hour [ $\pm 15$  minutes] after awakening)

- Drug dispensing for out-patient use
- Dispense outpatient PSQ and instruct patient to complete prior to the next scheduled visit

**Night 8  $\pm$  2 days (Visit 4)**

- Collect unused study drug and assess compliance
- Collect outpatient PSQ
- Urine pregnancy test for WOCBP, except those who have been postmenopausal for at least 1 year or are surgically sterile (result must be negative prior to dosing)
- Breathalyzer
- Pre-sleep questionnaire
- Review of concomitant medication
- Adverse event query
- Study medication administration (30  $\pm$  5 minutes prior to light off)
- PSG

**Day 9 (Visit 4)**

- Vital Signs (body temperature, respiratory rate, blood pressure, and pulse)
- Adverse event query
- Battery of tests (Post-sleep questionnaire, VAS, and DSST, in this order; one hour [ $\pm$  15 minutes] after awakening)
- Drug dispensing for out-patient use
- Dispense outpatient PSQ and instruct patient to complete prior to the next scheduled visit

**Night 22  $\pm$  2 days (Visit 5)**

- Collect unused study drug and assess compliance
- Collect outpatient PSQ
- Urine drug screen
- Urine pregnancy test for WOCBP, except those who have been postmenopausal for at least 1 year or are surgically sterile (result must be negative prior to dosing)
- Breathalyzer
- Pre-sleep questionnaire
- Review of concomitant medication
- Adverse event query
- Study medication administration (30  $\pm$  5 minutes prior to light off)

- PSG

